### Participant timeline {13}

See Table 1.

**Table 1 Tab1:**
[figure not shown]
Schedule of study procedures, outcomes, and visit windows

*GMI* Graded motor imagery

### Sample size {14}

The sample size calculation was based on a factorial analysis, where interventions are assumed to have independent effects. For the primary outcome of pain intensity at 16 weeks, we will be guided by a between-group difference of 1 point on an 11-point NRS to justify implementation of the interventions as suggested for chronic pain RCTs [55]. For the primary outcome of pain interference at 16 weeks, we will be guided by a between-group difference *T*-score metric of 5 to justify implementation of the interventions.

Using a repeated measures model with outcomes measured at baseline and follow-up timepoints, and with a correlation between adjacent time points of 0.7 [56], 182 participants are required to provide 90% power with a two-sided 2.5% significance level to detect an effect (of memantine compared to placebo, or graded motor imagery compared to no graded motor imagery) of either 1 point on an 11-point NRS for pain intensity, assuming a standard deviation of 2, or 5 *T*-metric points on the PROMIS Pain Interference scale, assuming a standard deviation of 10. Allowing for 10% dropout, we will aim to recruit a total of 204 participants (rounded up from 200.2).

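### The 182 participants stated for 90% power cannot be reproduced for the 16-week primary contrast from the inputs printed beside it

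*Protocol article*

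**What the plan says.** All the inputs are in the protocol article, Sample size {14}. The calculation starts from the factorial margins: "The sample size calculation was based on a factorial analysis, where interventions are assumed to have independent effects". The target differences are "1 point on an 11-point NRS for pain intensity, assuming a standard deviation of 2" and "5 *T*-metric points on the PROMIS Pain Interference scale, assuming a standard deviation of 10", both set for 16 weeks. The method is described as "Using a repeated measures model with outcomes measured at baseline and follow-up timepoints", "with a correlation between adjacent time points of 0.7". The result is that "182 participants are required to provide 90% power with a two-sided 2.5% significance level". Recruitment follows from it: "Allowing for 10% dropout, we will aim to recruit a total of 204 participants (rounded up from 200.2".

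Three other sections bear on the check:
- Trial design {8} allocates the four groups equally, so each main comparison is one half of the sample against the other.
- Primary outcomes (under Outcomes {12}) compares means at 16 weeks.
- Main analysis (under {20a}) describes a mixed model with three follow-up time points and the baseline value as a covariate.

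The scheduled follow-ups for the two primary measures are 16, 26 and 52 weeks. The Outcomes section adds a 12-week measurement of both for mechanism work, and a weekly pain score for the adherence analysis.

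**The concern.** The section gives an effect size, a significance level, a power and a correlation, then a sample size. A reader should be able to get from the first four to the fifth for the comparison the trial is about, and cannot. A correlation of 0.7 with baseline removes about half the outcome variance, yet 182 is only some 8% below the figure for an analysis that ignores baseline.

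What is at stake is the precision the trial was designed to deliver. General analysis principles puts the weight of interpretation on the size of the estimates and their confidence intervals. Depending on what lies behind 182, the effect detectable with 90% power may be well below the thresholds of 1 NRS point and 5 T-score points, or close to them. The printed paragraph does not let a reader tell.

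**Working it through.** **Inputs.** Standardised effect: 1/2 = 0.5 for pain intensity and 5/10 = 0.5 for pain interference. Two-sided 2.5%: z = 2.2414. Power 90%: z = 1.2816. Margins 1:1. Adjacent correlation 0.7.

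**Formula.** Total N = 4 × (2.2414 + 1.2816)² × v / 0.5², where v is the share of outcome variance left after using baseline. Since (3.523)² = 12.41, N = 198.6 × v. For baseline adjustment v = 1 − r²; for a change score v = 2(1 − r). Power at 182 is Φ(0.5 × √(182/(4v)) − 2.2414).

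**Attempt to reproduce 182 at 16 weeks**

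| Reading | v | N, normal | N, t-based | Power at 182 (normal) |
|---|---|---|---|---|
| Baseline-adjusted, r = 0.7 | 0.51 | 101.3 | 104 | 99.3% |
| Change score, r = 0.7 | 0.60 | 119.1 | 122 | 98.3% |
| Baseline-adjusted, r = 0.49 | 0.760 | 150.9 | 154 | 94.8% |
| Change score, r = 0.49 | 1.02 | 202.6 | 206 | 86.4% |
| Baseline not used | 1 | 198.6 | 202 | 87.1% (t-based 86.6%) |

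The value r = 0.49 is 0.7², which applies if the 12-week visit lies between baseline and week 16 and the correlation decays multiplicatively (AR(1)). None of the five rows gives 182.

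**Nearest coherent match.** Take AR(1) decay over baseline, 16, 26 and 52 weeks. Week 52 is then three steps from baseline: r = 0.7³ = 0.343, v = 0.882, N = 175.2 (t-based 178). That is close to 182, but it is a secondary time point. A few tests with several degrees of freedom also land within about 3% of 182, but none is the planned 16-week contrast.

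**What 182 would imply.** 182/198.6 = 0.9165, so 1 − r² = 0.9165 and r is about 0.29. Nothing in the document supports that value.

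**Detectable effect with 90% power**, taking 204 × 0.9 = 183.6 analysed, d = 3.523 × √(4v/183.6):
- r = 0.7: d = 0.371 SD, i.e. 0.74 NRS points or 3.7 T-score points.
- r = 0.49: d = 0.453 SD, i.e. 0.91 NRS points or 4.5 T-score points.
- Baseline not used: d = 0.520 SD, i.e. 1.04 NRS points or 5.2 T-score points.

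**Dropout.** 182 × 1.1 = 200.2, the printed figure. Recruiting that number and losing 10% leaves 200.2 × 0.9 = 180.2, short of 182. The inflation that preserves 182 is 182/0.9 = 202.2, so 203. The target of 204 leaves 183.6.

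**The case against.** The strongest reply is that the section never says the baseline-to-week-16 correlation is 0.7. It gives the correlation between adjacent time points and leaves the structure, the time points and the contrast unstated. Both primary measures are also collected at 12 weeks, and pain intensity weekly. Under a decaying structure the relevant correlation could be 0.49 or lower, and with close spacing the requirement moves towards the unadjusted 199. An article may also leave such detail to a fuller document, and the source cited for the correlation is not at hand.

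Much of this stands. A reader might infer that the correct sample size is 102 to 104 and that the trial really has 99% power. The document does not support that as the only answer: it is the direct reading for the planned model, and other readings are open. What the reply does not do is recover 182 for week 16. The section prints a result next to its inputs, and no 16-week reading tried connects them.

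A reader might also infer the opposite, that the trial is underpowered. The 87% figure needs an analysis that ignores baseline, whereas both the sample size paragraph and the main model use it. On the two baseline-adjusted readings tabulated, power at 182 is about 95% to 99%.

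Finally, the dropout slip has no practical effect, because the recruitment target exceeds the correctly inflated number.

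**Conclusion.** The point holds as a mismatch between stated inputs and stated result. For the 16-week primary contrast, 182 is not what the printed effect, significance level, power and correlation give. The direct reading needs about 101 to 104, the reading with an intervening 12-week visit about 151 to 154, and the reading without baseline about 199 to 202. Corresponding power at 182 is about 99%, 95% and 87%. The closest match found, about 175 to 178, belongs to week 52.

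These figures assume equal margins, a common SD, no interaction between the interventions, and no gain from the other covariates. The 0.49 reading also assumes AR(1) decay through week 12.

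The conclusion does not extend to which calculation the sponsor ran, or to inadequate power for the planned baseline-adjusted analysis. Enrolment is unaffected. The 200.2 is a wrong intermediate figure of no consequence for the target.

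**What to change.** Keep the recruitment target of 204. Re-run the calculation for the 16-week marginal contrast in the planned baseline-adjusted model. In the Sample size section, state the correlation structure, the time points included and the contrast sized. Then report what follows, either as power at the stated thresholds or as the effect detectable with 90% power. With 183.6 analysed, that effect is about 0.74 NRS points and 3.7 T-score points if the baseline-to-week-16 correlation is 0.7, and about 0.91 and 4.5 if it is 0.49. If 182 was derived for another time point or another test, say so.

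Do not insert a correlation near 0.3 merely to recover 182; an input should come from evidence and not from the answer.

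Replace 200.2 with 202.2 (182/0.9).

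The cost is one short calculation and a few sentences. Enrolment, conduct and the analysis model do not change.

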### Recruitment {15}

A decentralised design will be used to overcome barriers to participant recruitment common to CRPS trials, enabling nation-wide recruitment and increasing equity of access to all Australians, including those living in rural and remote geographical regions. We will use three strategies to recruit our target sample size: community-based advertisements using social media advertising (Facebook and Instagram); collaboration with primary and secondary care clinics; and collaboration with CRPS consumer and support groups. All potential participants will be directed to the study website (https://memoir.neura.edu.au/) where they will initiate eligibility screening.

## Assignment of interventions: allocation

### Sequence generation {16a}

The allocation sequence will be randomly generated a priori using Stata 14.0 software. Enrolled participants will be randomised to one of 4 intervention groups (1:1:1:1). The allocation sequence for memantine and placebo is a permuted block list consisting of blocks of randomly varying sizes, in equal proportion. The allocation sequence for the graded motor imagery and no graded motor imagery arms will be controlled by separate permuted block lists: one for memantine and one for placebo, each with blocks of randomly varying sizes, in equal proportion.

### Concealment mechanism {16b}

The pharmaceutical supply company (Eramol, UK) will be provided with the randomisation schedule. Eramol will package and label the study medication according to the randomisation schedule and seal the packages for transportation to the research pharmacy, Syntro (Melbourne, Australia). Each medication kit will be numbered randomly. A central web-based randomisation system (interface on Qualtrics software) will hold allocations to the graded motor imagery group. The blinding of the drug allocations provides additional concealment of the graded motor imagery allocation. These features will ensure that neither the person being randomised nor trial personnel are aware of the forthcoming allocation.

### Implementation {16c}

The allocation sequence will be generated by an independent statistician from the Australian National Health and Medical Research Council Clinical Trial Centre. The statistician responsible for the generation of the allocation sequence will not be involved in participant recruitment, treatment, data collection, or analysis. Only the National Health and Medical Research Council Clinical Trial Centre, drug manufacturer, and unblinded Data and Safety Monitoring Board (DSMB) statistician will hold the randomisation schedule. Trained research assistants will use the web-based randomisation system to inform eligible participants of their allocation to the graded motor imagery group.

## Assignment of interventions: blinding

### Who will be blinded {17a}

In this factorial trial, participants and study personnel will be blinded to memantine and placebo group assignment and unblinded to graded motor imagery assignment. As the CRPS Severity Score is the only clinician-assessed outcome, it will be evaluated by a clinician who is blinded to both treatment factors to minimise detection bias. All other outcomes are self-reported by participants and therefore unblinded for the graded motor imagery comparison. Blinding to memantine and placebo assignment will be maintained for the entire duration of the trial until all data have been collected and data analysis and interpretation have been completed. The independent statistician will be blinded to all intervention assignments until the preliminary analyses are complete (see General analysis principles).

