## Interventions

### Explanation for the choice of comparators {6b}

An inert placebo will be used as a comparator for memantine to separate the effect of this medicine from non-specific effects of being allocated and taking an oral medicine. Graded motor imagery will be evaluated against no graded motor imagery, as it was not considered possible to implement a sham that is both convincing and inert.

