#### Secondary outcomes

Pain intensity, assessed over the previous 7 days using the 11-point NRS. Collected at 26 and 52 weeks post-randomisation.Pain interference, assessed over the previous 7 days using PROMIS Pain Interference v1.1. Collected at 26 and 52 weeks post-randomisation.Physical function, assessed at present using PROMIS Physical Function v2.0 [42], with higher scores indicating greater physical function. Collected at 16, 26, and 52 weeks post-randomisation.Fatigue, assessed over the previous 7 days using PROMIS Fatigue v1.0 [43], with higher scores indicating greater fatigue. Collected at 16, 26, and 52 weeks post-randomisation.Self-efficacy to manage symptoms, assessed at present using PROMIS Self-Efficacy Manage Symptoms v1.0 [44], with higher scores indicating greater self-efficacy to manage symptoms. Collected at 16, 26, and 52 weeks post-randomisation.Cognitive function, assessed over the previous 7 days using PROMIS Cognitive Function Abilities Subset v2.0 [45], with higher scores indicating greater cognitive function. Collected at 16, 26, and 52 weeks post-randomisation.Depressive symptoms, assessed over the previous 7 days using PROMIS Depression v1.0 [46], with higher scores indicating greater depressive symptoms. Collected at 16, 26, and 52 weeks post-randomisation.Health-related quality of life, assessed over the previous 7 days and ‘generally’ using PROMIS Global Health short form v1.1 [47], with higher scores indicating better health-related quality of life. Collected at 16 and 52 weeks post-randomisation.Pain self-efficacy, assessed at present using Pain Self-Efficacy Questionnaire (two-item short form) (PSEQ-2) [48]. The PSEQ-2 comprises two 7-point Likert scales (total score = 14), with higher scores indicating higher pain self-efficacy. Collected at 16, 26, and 52 weeks post-randomisation.Patient Global Impression of Change [37], assessed at present using a 7-point scale, with higher scores indicating greater improvements. Collected at 16 weeks post-randomisation.CRPS severity, assessed at present using the CRPS Severity Score [49, 50]. The CRPS Severity Score assesses 8 self-report symptoms and 8 clinician-assessed signs (total score = 16), with higher scores indicating greater CRPS severity. Collected at 16 weeks post-randomisation.Cost effectiveness, assessed as prescription and over-the-counter medicines use and visits (yes/no) to a healthcare provider for CRPS. Collected via self-report questionnaires and MBS and PBS data at 16, 26, and 52 weeks post-randomisation.Adverse events, assessed as the number of participants with at least one adverse event, serious adverse event, or specific adverse event (yes/no). Collected during treatment and during follow-up.

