The coefficients in the model are conditional on the other factors in the model. However, our primary interest is in the estimation of the marginal effects of the interventions. Point and interval estimates of the marginal effect of each intervention at 16 weeks will be obtained by appropriately weighting the sum of the relevant model coefficients and the elements of the variance-covariance matrix using the -margins- command in Stata. Secondary outcomes and safety outcomes (the number of participants experiencing at least one adverse event, specific adverse events, serious adverse events) will be analysed in the same way except that log binary models will be used for binary outcomes. For each comparison, mean differences or risk ratios, each with 97.5% confidence intervals, will be presented in tables (see Supplementary Tables 2, 3, 4, and 5).

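### Half of the CRPS Severity Score is participant-reported and so unblinded for graded motor imagery, yet the blinding section sets the whole score apart as clinician-assessed

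*Protocol article*

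**What the plan says.** All references are to the protocol article.

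- **Composition of the score** (Outcomes {12}, Secondary outcomes): "The CRPS Severity Score assesses 8 self-report symptoms and 8 clinician-assessed signs (total score = 16". It is listed as one secondary outcome, collected at 16 weeks.
- **Who is blinded** (Who will be blinded {17a}): "participants and study personnel will be blinded to memantine and placebo group assignment and unblinded to graded motor imagery assignment".
- **How the score is classed** (same section): "As the CRPS Severity Score is the only clinician-assessed outcome, it will be evaluated by a clinician who is blinded to both treatment factors". The stated aim is to minimise detection bias.
- **The rule for self-report** (same section, next sentence): "All other outcomes are self-reported by participants and therefore unblinded for the graded motor imagery comparison".
- **Comparator** (Explanation for the choice of comparators {6b}): imagery is compared with no imagery, because "it was not considered possible to implement a sham that is both convincing and inert".
- **Analysis** (Main analysis): secondary outcomes "will be analysed in the same way except that log binary models will be used for binary outcomes". The article states no separate analysis of the signs or the symptoms.

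**The concern.** The blinding section gives a reason for calling an outcome unblinded: the participant supplies the answer and knows the imagery allocation. It then applies that reason to every outcome except the CRPS Severity Score. The outcomes section shows that the reason applies to half of that score as well.

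Blinding the clinician protects the judgement of signs. It does not protect the symptom items: a blinded clinician who asks about symptoms still records what an unblinded participant chooses to say.

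Both primary outcomes are self-reported and therefore open-label for imagery, so readers will look to the one clinician-assessed outcome for corroboration. If imagery lowers the total, the total alone cannot show whether the assessor-blinded signs moved, the unblinded symptoms moved, or both did. The article itself describes earlier imagery studies as being at high risk of bias, so the distinction bears on the question the trial sets out to settle.

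**Working it through.** **Step 1: reproduce the stated total.** Inputs from Secondary outcomes: 8 symptoms and 8 signs. 8 + 8 = 16, as stated. Self-reported share = 8/16 = 50%.

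**Step 2: apply the protocol's own rule to each half.**

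| Component | Source | Memantine vs placebo | Imagery vs no imagery |
|---|---|---|---|
| 8 signs (0–8) | Clinician blinded to both factors | Blinded | Assessor-blinded |
| 8 symptoms (0–8) | Participant | Blinded | Unblinded |
| Total (0–16) | Both | Blinded | Mixed, half and half |

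The inconsistency is confined to one cell: the symptoms in the imagery comparison.

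**Step 3: how a reporting shift would enter the total.** Suppose knowing the allocation changes the chance of endorsing each symptom by *b*, with no true effect. The symptom sub-score and the total both shift by 8*b*; the sign sub-score does not carry that shift. For *b* = 0.05, 0.10 and 0.15, the total shifts by 0.4, 0.8 and 1.2 points. These values of *b* are assumptions; the document gives none.

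**Step 4: illustration of scale, on assumptions that are not in the document.**

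- Item prevalence *p* = 0.7; correlation between items within a half, ρ = 0.1 to 0.3; correlation between the two halves, *r* = 0.3 to 0.5.
- From Sample size {14}: "182 participants are required to provide 90% power with a two-sided 2.5% significance level", so 182/2 = 91 per level of each factor.
- From Main analysis: "mean differences or risk ratios, each with 97.5% confidence intervals, will be presented in tables", so two-sided α = 0.025 and critical value 2.24.
- Unadjusted comparison of two means.

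Formulas: sub-score variance V = 8*p*(1 − *p*)(1 + 7ρ); total variance = 2V(1 + *r*); standard error = SD × √(2/91).

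Worked case, ρ = 0.1 and *r* = 0.3: V = 8 × 0.21 × 1.7 = 2.86; total variance = 2 × 2.86 × 1.3 = 7.43, SD 2.72; standard error 0.404. For a shift of 0.8, 0.8/0.404 = 1.98, and the interval excludes zero with probability about Φ(1.98 − 2.24) = 40%.

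Over the assumed range the SD of the total is 2.7 to 4.0, and:

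| Assumed shift in total | Chance the 97.5% interval excludes zero with no true effect |
|---|---|
| 0.4 | 6–11% |
| 0.8 | 19–40% |
| 1.2 | 42–77% |

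The nominal figure is 2.5%. The table shows only that modest shifts could matter. It is not evidence that such shifts will occur.

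**Step 5: precision cost of the sign sub-score, on the same assumptions.** If a true effect were spread equally over both halves, the standardised effect on the signs relative to the total would be √((1 + *r*)/2): √0.65 = 0.81 at *r* = 0.3 and √0.75 = 0.87 at *r* = 0.5. The sub-score is therefore somewhat less sensitive than the total, but still usable.

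**The case against.** **The article never calls the total a blinded outcome.** It says the clinician is blinded and that this minimises detection bias, and it openly gives the 8 + 8 composition. This stands. A reader might infer that the protocol claims full blinding of the score, and the text does not go that far. What it does do is set the whole score apart from the self-reported, unblinded outcomes, when its own definition supports setting apart only half.

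**Analysing the total of a published instrument is not an error.** This also stands, and the total should remain the planned outcome. The sub-score is proposed as support, not as a replacement.

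**Component results may appear in material not shown.** The Main analysis section refers to supplementary tables that are not available here. The point therefore rests on the outcome and classification that the article states, not on a claim that no component analysis exists anywhere.

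**The signs are not guaranteed free of bias.** The trial is fully decentralised, and the article does not describe how participants are kept from disclosing their allocation to the assessor. This stands as a caveat to attach to the sub-score.

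**A stronger reading is tempting:** that the signs are the only evidence on imagery free of participant reporting, every other outcome being self-report. The blinding section's wording invites that inference, but the outcomes section says healthcare use is drawn partly from Medicare and pharmaceutical benefits records, which participants do not report. The signs are the only clinician-assessed component, and no more should be claimed.

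**Conclusion.** The point holds within limits. Two sections of the article do not fit together: one defines the score as half self-report, and the other leaves it out of the self-reported, unblinded group. Exactly 50% of the score range is unblinded for the imagery comparison by the protocol's own rule, and this rests on no outside assumption.

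How much bias this causes, if any, is unknown; the shifts and percentages in the working are illustrations. The scope is one secondary outcome, at one timepoint, for one of the two factors. Memantine against placebo is not affected, because participants and assessor are both blinded to it. The primary outcomes do not use the score, and the article already acknowledges self-reported outcomes as unblinded for imagery.

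The change is still worth making. Without it, a difference in the total cannot be attributed to the assessor-blinded or the unblinded half, although the two can be separated in the analysis.

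**What to change.** 1. **Who will be blinded {17a}:** state that, for the imagery comparison, only the 8 sign items are assessor-blinded, and that the 8 symptom items are self-reported and unblinded.
2. **Secondary outcomes and Main analysis:** keep the 16-point total as the planned secondary outcome. Prespecify the 0–8 sign sub-score at 16 weeks, with the 0–8 symptom sub-score beside it, as a supportive analysis using the same modelling approach as the total.
3. **Interpretation:** note that blinding of the signs depends on participants not disclosing their allocation, and that the shorter range makes the sub-score somewhat less precise.

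The cost is a sentence or two of wording and a supportive row for each sub-score in a results table. The items are already part of the score, and neither the sample size nor the primary analysis changes. The Trial status section projects recruitment to Q2 2026 and analysis only after the last 52-week follow-up, so this can still be fixed before the definitive analysis with true allocations.
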